### Choice Context and Hypothesis

The study aims to identify the key considerations that American Indian men make when deciding about whether to get screened for PC. The choice context presented to the participants in the DCE will be framed as follows:

*Your doctor informs you that there is a blood-based test for PC, and that you are eligible for this test due to your age. Please consider the following scenarios. In which of these scenarios would you be more likely to test for PC?*

We hypothesize that American Indian men evaluate several screening attributes, such as mortality benefit, unnecessary biopsies, and treatment, as well as contextual factors, such as experiences with PC and the manner in which information is presented, when considering PC screening [25].

DCE choice tasks will resemble the task shown in Table 2. The sample task includes attribute levels identified in the literature review and several attribute levels hypothesized a priori to influence the choices of American Indian men; the selection of attributes and attribute levels in the actual DCE will be guided by the findings from phase 2. Columns represent screening options. Rows describe the attributes identified in phase 2. Cells represent feasible levels for each attribute. Each choice task involves the comparison of 2 hypothetical PC screening tests, followed by an “opt-out” question, that is, whether the participant would get tested in the preferred scenario, which reflects a realistic choice based on current USPSTF PC screening recommendations [10]. This opt-out option provides a reference point that allows for estimates of the potential uptake of PC screening. Prior to the choice tasks, participants will be introduced to each attribute, presented with *ceteris paribus* conditions (eg, the participant has insurance that covers the test), and will complete a training and comprehension task.

**Table 2. T2:** Example of discrete choice experiment choice task.

Attribute	Option A	Option B	Option C
Chance of identifying PC^a^ after it has spread	100 out of 1000 men like you would have PC diagnosed after it has spread	200 out of 1000 men like you would have PC diagnosed after it has spread	N/A^b^

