### Outcome Measure

#### Primary and Secondary Outcomes

The main survey outcome of interest is the PC screening uptake, and the main analytic outcome is the association between each attribute level and the probability of PC screening uptake. The secondary outcome, which is the tradeoffs that American Indian men are willing to make when deciding about PC screening, will be described in the form of mRS. Results will be used to estimate participants’ relative preferences for all potential combinations of attribute levels, that is, PC screening. Feasible strategies can be ranked in terms of expected PC screening uptake, providing concrete guidance on the acceptability of alternative scenarios, and prioritizing specific strategies to increase PC screening uptake in Lumbee men.

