#### DCE Data Analysis

We will analyze the choice data using mixed (random parameter) logit models [20]. The binary dependent variable will be 1 for the more preferred alternative and 0 for the other alternative in each choice task. The independent variables will be the effects-coded levels of each attribute. The mixed logit specification, estimated in STATA (StataCorp) version 16 or higher, allows for variation in preferences across respondents as well as error correlation across choice tasks within respondents. If we obtain more than 100 responses, we will also test latent class models to analyze the data, which may provide a better model fit. Latent class models will be estimated using Latent Gold Choice 5.0 software (Statistical Innovations).

The preference weights estimated using mixed logit models are the primary outcome of phase 3. Positive parameter estimates for effects-coded attribute levels indicate that an attribute level is more preferred compared to the mean, while negative parameter estimates indicate aversion. Tradeoffs will be described in the form of mRS.

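### The stated choice model compares only the two tests, so it cannot give predicted screening uptake or the size of level effects on uptake, which the article makes its main analytic outcome

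*Protocol article*

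**What the plan says.** **Outcomes.** Primary and Secondary Outcomes states: "The main survey outcome of interest is the PC screening uptake". It then says that "the main analytic outcome is the association between each attribute level and the probability of PC screening uptake". It adds: "Feasible strategies can be ranked in terms of expected PC screening uptake". Marginal rates of substitution are secondary.

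**Task.** The prose of Choice Context and Hypothesis describes a choice between two hypothetical tests, then a question on whether the man would be tested in the scenario he preferred. Its purpose is given: "This opt-out option provides a reference point that allows for estimates of the potential uptake of PC screening". Table 2, which the actual tasks are to resemble, instead shows Options A, B and C side by side. C is no screening, and a single response row covers all three.

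**Model.** DCE Data Analysis specifies a mixed logit: "The binary dependent variable will be 1 for the more preferred alternative and 0 for the other alternative in each choice task". It continues: "The independent variables will be the effects-coded levels of each attribute". It then names the primary quantity: "The preference weights estimated using mixed logit models are the primary outcome of phase 3". Sample Size and Statistical Power counts two alternatives per task (a=2).

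**The concern.** The opt-out answer is collected for one declared purpose, estimating uptake, but it does not appear in the model as described. The outcome is binary, the alternative to the preferred one is singular, and the regressors are attribute levels only. Such a model describes which of two tests men like better. It does not describe whether they would be tested.

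At stake is the main analytic outcome. A level that makes one test more attractive than another may move many men from not testing to testing, or almost none, depending on how willing they are to test at all. The stated model holds no information on that willingness. The two sections also name different primary quantities, association with the probability of uptake and preference weights, so the text does not settle which one the study will be judged on.

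**Working it through.** **1. The plan's own figure.** Rule: n·t·a/c ≥ 500, with t=10, a=2 and c=4 (Sample Size and Statistical Power). For n=100: 100 × 10 × 2 / 4 = 500. The minimum n is 500 × 4 / (10 × 2) = 100. The stated 100 reproduces, and it does so with the opt-out not counted as an alternative.

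**2. Why the constant cancels.** Let V_A and V_B be the attribute-based utilities of the two tests and k a constant for testing versus not testing. Then

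P(A over B) = 1 / (1 + exp(−[(k + V_A) − (k + V_B)])) = 1 / (1 + exp(−[V_A − V_B])).

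k drops out. In a mixed logit this holds for each draw of the random parameters, so it also holds after averaging.

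**3. Illustration by simulation.** Assumed inputs: 100 respondents, 10 tasks, 5 attributes and fixed illustrative coefficients. The same A-versus-B choices were combined with five true values of k. Uptake here means that the preferred test beats no test. The two answers share one utility scale by construction.

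| True k | Two-alternative log-likelihood | Simulated uptake | k fitted once the opt-out is modelled |
|---|---|---|---|
| −2 | −540.108 | 25.7% | −2.11 |
| −1 | −540.108 | 45.6% | −1.10 |
| 0 | −540.108 | 68.4% | −0.02 |
| 1 | −540.108 | 83.8% | 0.94 |
| 2 | −540.108 | 92.6% | 1.89 |

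The two-alternative fit is identical in every row, while uptake runs from about a quarter to over nine tenths. With the opt-out as a third alternative, k is recovered.

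**4. Size on the probability scale.** For a weight difference of 0.5 logits and baseline uptake p, the change is expit(logit(p) + 0.5) − p:

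- p = 0.500: 0.622 − 0.500 = +12.2 points
- p = 0.202: 0.294 − 0.202 = +9.2 points
- p = 0.954: 0.972 − 0.954 = +1.8 points

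The last two baselines are 1 − 0.798 and 1 − 0.046, from the no-screening shares that Table 1 reports for the Australian and US study of 302 men and the French study of 1008 men. They show a range and are not forecasts for Lumbee men. The 0.5 is an assumed difference.

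**5. What happens to the ranking.** With one k and the same weights for everyone, uptake = expit(k + V) rises with V, so ranking by utility equals ranking by uptake for any k. With the normally distributed random parameters planned under Experimental Design and Choice Set Construction, this is not guaranteed. Assumed example: strategy X has V ~ N(0, SD 0.5) and strategy Y has V ~ N(0.2, SD 1.5).

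| k | Mean uptake X | Mean uptake Y |
|---|---|---|
| −2 | 12.9% | 21.4% |
| +2 | 87.1% | 83.2% |

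The order reverses with k, which the stated model cannot estimate.

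**6. Sample size if the opt-out is counted.** With a=3: 500 × 4 / (10 × 3) = 66.7, so n ≥ 67. At n=100 the rule gives 100 × 10 × 3 / 4 = 750, above 500.

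**The case against.** **The analysis plan may supply the missing term.** The article condenses a fuller plan, and a constant or the handling of a follow-up question is often left to it. This stands as far as silence goes. But the article is not merely silent: it fixes a binary outcome with one other alternative and attribute-only regressors, and it counts a=2. Those statements conflict with the outcome and with the stated purpose of the opt-out.

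**Coding 1 for chosen and 0 for not chosen is the usual layout even when a no-choice row is present, and Table 2 shows three options.** This is fair. The two-alternative reading is the more natural one for DCE Data Analysis, but not the only one the article allows. If three alternatives were meant, the wording and a=2 still need correcting. Attribute levels alone also would not define the utility of Option C, which is marked not applicable on two of the four attributes in Table 2.

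**A reader might infer that the study cannot report uptake at all, or cannot rank strategies.** The documents do not support that. The opt-out answers are collected, so raw uptake in preferred scenarios can be tabulated without a model. Preference weights and marginal rates of substitution come from the two-alternative model unharmed. The direction of each level's effect and the ranking of strategies also carry over if one constant and the same weights govern the decision to test and heterogeneity does not reorder the strategies.

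**The two primary quantities are close relatives.** A preference weight is an association on the utility scale, so this is loose wording more than a separate contradiction. It still matters here, because the step from weight to probability is the one that the stated model cannot take.

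**Conclusion.** The point holds in a bounded form. The model as stated cannot give predicted uptake, nor the size of the quantity that the article calls its main analytic outcome, "the association between each attribute level and the probability of PC screening uptake". One and the same weight difference of 0.5 logits is compatible with anything from +1.8 to +12.2 points over the baselines shown.

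The cancellation is algebraic and needs no assumption beyond a constant common to both tests. The point sizes assume a plain logit for test versus no test, with the A-versus-B weights carrying over unchanged. The simulation and the reversal example use illustrative values.

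This is an error of specification, and no data are lost. The article reports that no participant had yet been recruited to the DCE, so it can be corrected before fielding. It should be, because the main analytic outcome depends on it.

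**What to change.** 1. Reconcile the task format: a pair followed by an opt-out question (prose of Choice Context and Hypothesis) or a simultaneous A/B/C choice (Table 2). This decides how the data can be coded.
2. Rewrite DCE Data Analysis so that the opt-out answer enters the primary model. One way is a third alternative with an opt-out constant as a random parameter. Under the two-step format the two answers are then recoded jointly, and the assumption that they share one utility scale is stated and checked. The other way is a separate model of the would-test answer.
3. Compute uptake and level effects on uptake from that model. Keep the A-versus-B model as supporting.
4. Optimise the experimental design for the model actually used, and make the count of alternatives in the sample-size section match. With a=3 the rule needs n ≥ 67, so 100 still meets it.
5. Name the same primary quantity in Primary and Secondary Outcomes and in DCE Data Analysis.

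Cost: in the three-alternative version, one extra mean and one extra SD to estimate; in either version, minor edits to the design specification and text before fielding. There are no new survey items and no larger sample under the article's own rule. If the simultaneous format is chosen, tasks answered with the opt-out give no A-versus-B information, and this should be weighed when settling step 1.

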### Ethical Considerations

This study has been approved by the IRB of Wake Forest University School of Medicine (IRB00084519). We will seek approval from the Lumbee Tribe’s IRB for the DCE phase as well as official approval to start data collection from the Lumbee Tribe. One of the team members of this study is a member of the Lumbee Tribe IRB and will serve as a liaison between the study team and the IRB. The Lumbee Tribe IRB was set up after our study began. All phases of the research study that involve human participants will be conducted in accordance with the Declaration of Helsinki and the Belmont Report. All identities of the participants’ survey and IDI data will be blinded to the research team to ensure anonymity. In phases 2 and 3, Lumbee men will provide informed consent to participate in the study. We will also use Indigenous Data Sovereignty Principles and acknowledge that the Lumbee Tribe is the ultimate authority on how the research is conducted [41]. We also acknowledge that the Lumbee Tribe is an equal partner in this project. All surveys will be confidential and will not contain any identifying information. Regarding the qualitative formative work, all participant references to specific people and places will be replaced with “xx” to ensure anonymity. Data will be transferred through the use of the Health Insurance Portability and Accountability Act–compliant Box cloud software (Box Inc). Participants will receive $50 remuneration for participating in the formative qualitative work. Participants will receive $30 for completing the DCE survey.

## Results

The project was funded in 2024 by the Donaghue Foundation Greater Value Program. The project is anticipated to start data collection in April 2026 and end in June 2026. We have not recruited any participants as of yet into the DCE study. We expect the results to identify preferences of American Indian men that impact PC screening using PSA that would enable future researchers and providers to tailor culturally responsive interventions to increase PC screening in this population. All results from the qualitative formative interviews and the DCE will be shared with the Lumbee Tribe prior to submission to peer-reviewed journals.

## Discussion

### Overall Contribution

This study will be the first to use DCE methods to inform the development of preference-concordant screening strategies aimed at reducing the PC mortality disparity among American Indian men in the United States. We chose to focus on the Lumbee Tribe due to multiple factors. First, American Indians are an underrepresented group in PC research. Second, the Lumbee Tribe is located primarily in rural southeastern North Carolina; rural areas are disproportionately impacted by cancer mortality [5]. Although rural areas in the United States have lower cancer incidence than urban areas, cancer mortality is higher in rural areas [42]. Third, prior work has identified that American Indian men in North Carolina are at higher risk for dying because of PC than other racial and ethnic groups, possibly due to seeking care when their PC is at a more advanced stage. Therefore, new approaches to PC screening are needed. Fourth, this is the first study to tailor a DCE on cancer screening using culturally responsive approaches, and it is being driven by members of the Lumbee Tribe who are cancer prevention researchers (RB, TL). This DCE is the first of its kind and will advance what is known about PC screening beliefs and practices of American Indian men. Estimates from our study will inform provider-patient communication and provider behaviors in PC screening consultations with American Indian men. The findings of this study can be used to design preference-concordant screening strategies and pragmatic trials that compare the effectiveness of different options and incentives to increase PC screening.

### Dissemination of Findings

Prior to submitting the findings of phases 2 and 3, we will inform the Lumbee Tribe of our findings and ask for permission to submit the report to a peer-reviewed journal, in accordance with Indigenous Data Sovereignty Principles [41]. We acknowledge that the Lumbee Tribe has the ultimate authority over where and how research findings that relate to the Lumbee Tribe are disseminated and respect that principle.

Prior DCEs investigating PC screening have found that, among the attributes studied, decreasing one’s chances of dying because of PC is the most important attribute. We hypothesize that the results from this study will be consistent with that principal finding. Our study, however, will provide a culturally responsive approach to PC screening among American Indian men. The information from our study will inform future interventions with providers and American Indian men to increase PC screening.

The strength of our study is that it is being developed in collaboration with and under the approval of the Lumbee Tribe of North Carolina, one of the largest tribes in the eastern United States. The area in which members of the Lumbee Tribe reside is also rural, providing one of the first estimates of, which we are aware of, PC screening preferences in this population.

Like all studies, our DCE has limitations. First, indigenous tribes are incredibly diverse, and the findings from one tribe are not expected to apply to other tribes. Second, the low expected sample size precludes any possibility of investigating preference heterogeneity and latent class analysis. Additionally, while our attributes and approach have been guided by formative qualitative interviews, there may be other aspects that inform preferences of American Indian men in PC screening that were not captured and thus excluded from our DCE.

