While PSA screening has largely fallen out of favor in primary care settings for men with average PC risk, the Prostate Cancer Foundation and the American Urological Association recommend providers to conduct a baseline PSA test for Black men aged between 40 and 45 years and proceed to obtain annual PSA testing if PSA level is at or above 2 ng/mL [11], in contrast to current USPSTF guidelines [12]. The USPSTF guidelines, which are based on the Prostate, Lung, and Colorectal study, do not differentiate between high-risk men and average-risk men, and Black men are not included in their results. So, there is a general misunderstanding about the true sensitivity or specificity of the PSA. Currently, American Indian men are not identified by any organization as a high-risk population for PC, despite experiencing significantly worse outcomes than other racial and ethnic identities.

PSA-based PC screening is considered a preference-sensitive decision because there are multiple medically acceptable options [13]. Preference-sensitive decisions require providers to share the options that patients may have, their risks and benefits, and use SDM to arrive at a decision. Since patient input is required and patients are supposed to share their preferences in these situations, role preferences during medical encounters play an outsized role in these preference-sensitive decisions [14]. However, few studies that investigate patient preferences routinely take into account patients’ role preferences during medical encounters [15].

Persistent disparities in PC mortality due to underscreening, disparities in accessing treatment among American Indian men, and PC diagnoses at later stages of the disease suggest that new approaches are needed to reduce PC mortality in this population. However, less information is known about PC screening preferences, especially in the American Indian population. To understand and address disparities in PC screening rates and outcomes, it is important to study American Indian men’s preferences regarding this important screening test. Discrete choice experiments (DCEs) are routinely used to elicit and quantify preferences for health care decisions, including screening options for cancers and treatments in various real-world scenarios [16,17]. This makes DCE an excellent option to study PC screening preferences.

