This study describes our study protocol for a research study aimed at identifying PC screening strategies that align with the preferences of American Indian men and also identifying key tradeoffs. To the authors’ knowledge, this study would be the first to use a culturally responsive approach to develop and field DCE. DCEs offer a novel approach that evaluates how PC screening characteristics interact with individual characteristics and preferences for designing targeted PC screening strategies.

The aims of this protocol report are as follows:

Conduct a literature review, followed by qualitative, culturally responsive formative research with American Indian men to develop a comprehensive understanding of facilitators and barriers to PC-related communication, explore role preferences in PC-related SDM, and prioritize preference-relevant features of PC screening strategies;Develop and field a DCE survey to elicit the PC screening preferences of American Indian men and identify barriers to and facilitators of PC screening uptake; andIdentify feasible, culturally appropriate, preference-concordant screening strategies targeted for American Indian men.

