Multimedia Appendix 1) [22-26]. There was a median of 6 attributes included in the 5 studies. Table 1 presents the key characteristics of each included study. The most important attribute among all studies was reducing the risk of dying from PC. In the studies that examined an opt-out option (3/5, 60%), which is a realistic choice, most men preferred not to have PC screening in 2 studies [23,26]. In the Charvin et al [23] study, which included an educational video about PSA-based screening, those randomized to the video significantly preferred no screening to getting screened. Howard and colleagues [25] also found that younger men valued preventing PC mortality more than older men, highlighting the need to integrate preference heterogeneity into future studies. Attributes that decreased the likelihood of getting screened for PC included higher risks of needing a biopsy and higher risks of adverse treatment effects. Finally, Pignone and colleagues [26] found that different value clarification methods produced different results on PSA screening decisions; that is, those who received a balance sheet are significantly more likely (*P*<.001) to choose PC screening (43.7%) than a rating and ranking method (34.2%) or DCE (20.2%). However, there was no statistically significant difference between the different methods (balance sheet, rating and ranking, and DCE) on *intention* to undergo PC screening. An important finding of the Pignone study is that when men were presented with unlabeled test options, they most often chose the no screening option. Whereas in the labeled item about whether they intended to get screened for PC, the men chose they intended to get screened. These studies collectively report that most men would prefer not to undergo PC screening given the risks of overdiagnosis and overtreatment. However, the studies also collectively suggest that men are willing to accept tradeoffs such as false positives and overdiagnosis if it means their PC is caught at an early stage.

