#### Supplemental Survey

Participants will also complete a survey that assesses potential correlates of preferences. The survey will elicit sociodemographic characteristics (eg, age), health-related quality of life, trust in providers, decisional control preferences, and fatalism (see phase 2).

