#### Sample Size and Statistical Power

Based on our past experience and DCE sample size recommendations, which combine the number of respondents (n), choice tasks (t=10), alternatives per task (a=2), and the maximum number of feature levels (c=4), and established a cutoff (nta/c≥500), we calculated that a sample size of 100 participants will provide sufficient power to characterize mean preferences for PC screening [39].

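### The limitations rule out any study of preference heterogeneity at n=100, while the design, model and survey sections of the same protocol plan for it

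*Protocol article*

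**What the plan says.** All references are to the protocol article.

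- **Limitations (under Dissemination of Findings):** "the low expected sample size precludes any possibility of investigating preference heterogeneity and latent class analysis".
- **Experimental Design and Choice Set Construction:** the design is optimised for a mixed multinomial logit, expressly to build in heterogeneity. The model is a panel random parameter logit with normally distributed parameters and 500 Halton draws.
- **DCE Data Analysis:** the mixed logit lets preferences differ between respondents. Latent class models will also be tried if there are more than 100 responses. On covariates: "The independent variables will be the effects-coded levels of each attribute".
- **Supplemental Survey:** "Participants will also complete a survey that assesses potential correlates of preferences". It lists quality of life, trust in providers, decisional control preferences, fatalism and sociodemographic items.
- **Background:** the Introduction says that "role preferences during medical encounters play an outsized role in these preference-sensitive decisions", and that the DCE approach "evaluates how PC screening characteristics interact with individual characteristics and preferences for designing targeted PC screening strategies". The literature review describes an earlier study's age result as "highlighting the need to integrate preference heterogeneity into future studies".
- **Sample Size and Statistical Power:** "a sample size of 100 participants will provide sufficient power to characterize mean preferences for PC screening".

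**The concern.** A reader cannot tell from this text whether heterogeneity will be studied. One section says it is impossible, two are built around it, and a third collects data whose stated use is to explain it.

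An article may leave covariate detail to an analysis plan. Here the text does more than stay silent: it declares the analysis impossible.

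Three things are at stake:

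- The random-parameter SDs, which are estimates of heterogeneity, may go unreported because the limitations disown them.
- The trust, control and fatalism items are asked of participants with no stated use in the DCE analysis.
- If the correlates are examined after all, the choice among several of them would be made after the data are seen.

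**Working it through.** **1. The plan's own figure.** The sample-size rule uses "choice tasks (t=10), alternatives per task (a=2), and the maximum number of feature levels (c=4), and established a cutoff (nta/c≥500". So n = 500 × c / (t × a) = 500 × 4 / (10 × 2) = 100, which reproduces exactly and with no margin. The text does not say whether the two attention tasks fall inside the ten. If they do, t = 8 and the rule gives 500 × 4 / (8 × 2) = 125.

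**2. What the rule says about subgroups.** For 50 men, nta/c = 50 × 10 × 2 / 4 = 250, half the cutoff. Separate preference weights by subgroup are therefore not supported. That part of the limitation is sound.

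**3. The latent class condition.** Fielding assumes 400 × 0.25 = 100 completed surveys, and latent class models start above 100. One response more than expected triggers an analysis that the limitations call impossible.

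**4. Is a person-level contrast in uptake out of reach?** The documents give no alpha, power, split, uptake or within-man correlation. I assume two-sided 0.05, and 80% power where a detectable difference is quoted.

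*One would-test answer per man.* The formula is n per group = [1.96√(2p̄(1−p̄)) + 0.842√(p₁(1−p₁)+p₂(1−p₂))]² / (p₂−p₁)². For 50% versus 70%: [1.96√0.48 + 0.842√0.46]² / 0.04 ≈ 93 per group, against 50 available. With 50 per group the detectable difference is 25–28 points for lower-group uptake of 20–60%. It is 28–34 points at a 20/80 split.

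*Repeated answers.* With m answers per man, effective n per group = 50 × m / (1 + (m−1) × ICC). For m = 10, from 50% uptake:

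| ICC | Effective n per group | Detectable difference |
|---|---|---|
| 0.3 | 500/3.7 = 135.1 | 17 points |
| 0.5 | 500/5.5 = 90.9 | 20 points |
| 0.7 | 500/7.3 = 68.5 | 23 points |
| 0.9 | 500/9.1 = 54.9 | 26 points |

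*Simulation.* A random-intercept logit was simulated with 10 answers per man and lower-group uptake of 50%. The men's yes-shares were compared by t test. Power, good to a point or two:

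| Contrast | Between-man SD (logit) | 50/50 | 30/70 | 20/80 |
|---|---|---|---|---|
| 15 points | 1.0 | 85% | 77% | 62% |
| 17 points | 1.5 | 82% | 72% | 58% |
| 19 points | 2.5 | 76% | 66% | 52% |

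With 8 answers the 50/50 figures are about 83%, 80% and 74%. At SD 2.5 a 15-point contrast has only about 55% even at 50/50. A 25-point contrast has about 78% or more at 20/80 for SD 1.5 to 2.5. A 10-point contrast is never adequately powered: at 50/50 it has about 51% at SD 1.0 and less at larger SDs.

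**5. Can the stated model deliver this?** Choice Context and Hypothesis collects a would-test (opt-out) answer in each task in order to estimate uptake. DCE Data Analysis codes only the preferred alternative against the other one and states no opt-out constant. A person-level term on uptake needs that constant first.

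**The case against.** The strongest reply is that the study is sized for mean preferences and its primary and secondary outcomes are mean attribute effects and trade-offs, so declining heterogeneity analysis is consistent with its scope. That stands as a reason to keep any such analysis exploratory. It does not explain why the design and model sections plan for heterogeneity.

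A reader might infer that the model ignores differences between men. It does not: the mixed logit has respondent-level random parameters. Only observed traits are absent.

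A reader might also infer that a stated purpose has been abandoned, or that the study repeats the neglect of role preference it criticises. The documents do not support that. The Introduction's sentence on interaction with individual characteristics describes what DCEs offer, and none of the three aims names analysis by personal trait. The third aim targets American Indian men as a population. Role preference is assigned to the formative phase, where it is explored in line with the first aim and summarised descriptively. The literature review's remark on heterogeneity follows from one earlier study's age result.

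The power figures rest on assumptions, and nothing shows that control preference would split evenly. That also stands, which is why the unequal splits are shown. Finally, a contrast in overall uptake is not an attribute-by-trait interaction, and such interactions remain out of reach.

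**Conclusion.** The inconsistency is real and should be resolved before fielding. The limitation contradicts the heterogeneity-optimised design, the random-parameter model, the conditional latent class plan and the stated purpose of the supplemental survey.

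The exclusion is right for subgroup-specific weights, attribute-by-trait interactions and small contrasts. It is too broad for one or two large, pre-named contrasts in uptake. A reader might take the 50/50 results as showing that n=100 comfortably detects 15 to 19 points; the unequal splits and the larger SDs show that it does not. Only contrasts of about 25 points are reasonably robust over the range examined. Everything about power depends on assumed alpha, split, uptake and between-man SD, and on the would-test answer entering the model.

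**What to change.** 1. **Limitations.** Reword so that the sample size rules out subgroup-specific preference weights and small person-level contrasts only. Make the latent class statement agree with the conditional plan in DCE Data Analysis.
2. **DCE Data Analysis, random parameters.** State that the estimated random-parameter SDs will be reported with 95% intervals.
3. **DCE Data Analysis, opt-out and covariates.** State that the would-test answer enters the model with its own constant, and amend the coding of the dependent variable to match. Pre-name at most two exploratory interactions with that constant: decisional control preference and trust in provider. Report them with 95% intervals and no confirmatory claim.
4. **Detectable size.** Give it with its assumptions, including an unequal split.

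The cost is a few lines of text plus the change to the outcome coding, with no new data. DCE recruitment had not begun when the article was written, so the terms can still be named before data are seen. The downside is wide intervals, so the results can only be exploratory.
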